### 3 Definition of Reportable Events

The following adverse events are considered "serious reportable adverse events:"

- Death of a subject or life threatening events.
- Hospitalization (other than elective procedures or outpatient observation of <24 hour duration) or prolongation of hospitalization.
- Cancer or congenital anomaly.
- Chronic or permanent disability.
- Overdose.
- Any serious adverse event (i.e., an adverse event that is graded as serious or life-threatening in appendix 2).

## APPENDIX 2

### Table for Grading Severity of Adult Adverse Experiences for Vaccine Trials

#### Guidelines

ABBREVIATIONS: Abbreviations utilized in this Table include:

|                |                             |     |                        |
|----------------|-----------------------------|-----|------------------------|
| ULN            | =Upper Limit of Normal      | LLN | =Lower Limit of Normal |
| R x | =Therapy                    | Req | =Required              |
| Mod            | =Moderate                   | IV  | =Intravenous           |
| ADL            | =Activities of Daily Living | Dec | =Decreased             |

#### ESTIMATING SEVERITY GRADE

For abnormalities NOT found elsewhere in the Toxicity Table use the scale below to estimate grade of severity:

|         |                   |                                                                                                                                                               |
|---------|-------------------|---------------------------------------------------------------------------------------------------------------------------------------------------------------|
| GRADE 1 | Mild              | Transient or mild discomfort (< 48 hours); no medical intervention/therapy required.                                                                          |
| GRADE 2 | Moderate          | Mild to moderate limitation in activity – some assistance may be needed; no or minimal medical intervention/therapy required.                                 |
| GRADE 3 | Severe            | Marked limitation in activity, some assistance usually required; medical intervention/therapy required, hospitalization possible.                             |
| GRADE 4 | Life- threatening | Extreme limitation in activity, significant assistance required; significant medical intervention/therapy required, hospitalization or hospice care probable. |

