## **2.4 Inclusion Criteria**

- Healthy adult aged 18-55 years.
- Normal medical history and physical examination.
- Normal urine dipstick, blood count, liver enzymes, and creatinine.

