## **2.7 Immunisation**

On Day 0, subjects will receive a single intradermal injection of 0.1ml BCG over the deltoid muscle. Vital signs will be monitored at 30 and 60 minutes post-immunisation. Local reactions at the site of administration will be evaluated at 60 minutes.

A photograph of the injection site may be taken at 48 hours (with written consent). The injection site will be reviewed 7 days after each immunization.

Blood will be taken at the following time points: At the screening visit\*, prior to the vaccination, 1 week after the first vaccination\*, 2 weeks, 4 weeks, 8 weeks, 12 weeks\* and 24 weeks after the vaccination. Up to 55 mls will be taken at any one time with the total being no more than 500 mls over the study period. \*Samples taken on these dates will be tested for full blood count and biochemical screen. Immunological assays will be performed at all time points to determine vaccine immunogenicity. A pregnancy test will be performed prior to vaccination for female volunteers. Peripheral blood mononuclear cells will be prepared for cellular immunological assays to be performed without or following cryopreservation. Other serological measures of immune response, i.e. antibody titres, will be assayed on frozen plasma samples.

All blood tests will be taken within 1-3 days of the due date as described in the schedule above.

At the 24 week timepoint, a Heaf test will be repeated in order to document the change (if any) in Heaf responsiveness after the second BCG vaccination.

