#### SERIOUS OR LIFE-THREATENING Adverse Events

ANY clinical event deemed by the clinician to be serious or life-threatening should be considered a Grade 4 Adverse Event. Clinical events considered to be serious or life-threatening include, but are not limited to: seizures, coma, tetany, diabetic ketoacidosis, disseminated intravascular coagulation, diffuse petechiae, paralysis, acute psychosis, severe depression.

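### In the text shown, Appendix 2 has no cut-offs for the blood count or creatinine, and its fallback scale cannot grade an untreated, symptom-free laboratory abnormality above mild

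*Protocol*

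**What the plan says.** Protocol section 2.7 marks three blood samples for safety testing: screening, week 1 and week 12. Of these it says: "Samples taken on these dates will be tested for full blood count and biochemical screen". The contents of the biochemical screen are not listed. Section 2.4 makes the blood count and creatinine part of eligibility: "Normal urine dipstick, blood count, liver enzymes, and creatinine".

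Appendix 2 grades severity. Its laboratory pages run from potassium to lipase, and a later page adds urine protein and blood in the urine. For anything without a row, the part headed ESTIMATING SEVERITY GRADE instructs: "For abnormalities NOT found elsewhere in the Toxicity Table use the scale below to estimate grade of severity".

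Two other places bear on severity. Section 1 of Appendix 1 gives a mild, moderate and severe scale. Section 3 of Appendix 1 lists reportable serious events, and its last item refers to the grade given under Appendix 2.

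**The concern.** The protocol collects a full blood count for safety but, in the text shown, gives no numeric rule for its severity. It does not leave the question open: it sends unlisted abnormalities to a scale built for symptoms. A fall in neutrophils or platelets, or a rise in creatinine, often causes no discomfort and no loss of activity, so the scale does not register how far the value has moved.

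Two things are at stake. First, severity would mean different things within one safety summary: a potassium result is graded by its number, a platelet count by how the volunteer feels. Second, because the Appendix 2 grade is one route into the reportable-event definition, a blood count abnormality lacks a route that other laboratory values have. Safety is half of the study objective in section 2.1, so how abnormalities are graded is not incidental.

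**Working it through.** No arithmetic applies; the protocol states no figure to reproduce. The check sets the table rows against the tests performed, then reads the fallback literally.

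**Step 1: rows present.** The blood chemistry rows are potassium, phosphate, calcium, magnesium, bilirubin, glucose, triglycerides, uric acid, AST, ALT, GGT, alkaline phosphatase, amylase, pancreatic amylase and lipase: 15 parameters. Proteinuria and hematuria are graded under urinalysis. Rows for haemoglobin, white cells, neutrophils, lymphocytes or platelets: 0. Rows for creatinine: 0. The nearest entry, under cardiovascular, grades bleeding and transfusion, not a count.

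**Step 2: how listed values are graded.** By number alone. Potassium above 6.5 meq/L is Grade 4, as is lipase above 5.0 x ULN, whatever the volunteer feels.

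**Step 3: how unlisted values are graded.** Take a marked fall in platelets at week 1 in a volunteer who feels well and is given nothing.

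- Grade 1: "Transient or mild discomfort (< 48 hours); no medical intervention/therapy required". The intervention clause is met; the discomfort clause is not.
- Grade 2 requires limited activity, with "some assistance may be needed; no or minimal medical intervention/therapy required". Activity is not limited.
- Grade 3: "Marked limitation in activity, some assistance usually required; medical intervention/therapy required, hospitalization possible". Neither part is met.
- Grade 4: "Extreme limitation in activity, significant assistance required; significant medical intervention/therapy required, hospitalization or hospice care probable". Neither part is met.

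All four grades open with discomfort or limited activity, all four carry an intervention clause, and none carries a laboratory cut-off. With the clauses read together, the platelet fall satisfies no grade strictly and is closest to Grade 1. Reading the clauses as alternatives does not help: absence of treatment would then satisfy Grades 1 and 2 alike for every untreated event, and the size of the fall would still play no part.

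**Step 4: other routes.**

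- The Appendix 1 scale also rests on discomfort and daily activities, with no laboratory thresholds.
- The override in Appendix 2 reads: "ANY clinical event deemed by the clinician to be serious or life-threatening should be considered a Grade 4 Adverse Event". It is worded for clinical events, so its reach to a bare laboratory value is arguable. It leads only to Grade 4 and gives no way to assign Grade 2 or 3.
- Appendix 2 notes that some protocols may add grading criteria of their own. The text shown adds none for these tests.

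**Step 5: consequence.** A potassium above 6.5 meq/L falls in the potentially life-threatening column on its number, and so has a route to the last item of the reportable list. A blood count value has no such numeric route.

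**The case against.** The strongest case on the other side has five parts.

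- **Other laboratory values can be graded above mild.** True. An ALT of 8 x ULN is Grade 3 as written. A reader might infer from the gap that the trial could report no laboratory abnormality above mild whatever the values were. The table's 15 chemistry parameters contradict that.
- **The fallback is not only about symptoms.** True. Every grade has an intervention clause, and Grades 3 and 4 mention hospitalization. A symptom-free abnormality that needs treatment might be read as Grade 3 or 4. The scale does not say whether its clauses are joint or alternative, although other rows use an explicit OR. The point therefore holds for untreated, symptom-free abnormalities only.
- **Post-vaccination creatinine is inferred.** True. It is named only as an entry test, and the screen is not itemised. Sodium might seem an equal omission, but the protocol never names it, so no claim is made. The blood count needs no inference.
- **Rows may have been lost when the text was read.** Possible. LLN and Dec are defined as abbreviations used in the table, yet no row shown uses them, and Appendices 3 and 4 are cited but not in the text. Against this, the first laboratory page runs straight from its header to potassium, and removal of rows when the table was modified would explain the unused abbreviations equally well. This cannot be settled from the text.
- **The practical weight is limited.** Partly true. Eligibility uses normal values, not grades. Section 2.8 names no laboratory endpoint, and no stopping rule depends on a grade. The numerical results are still collected, death, life-threatening events and hospitalization are reportable without a grade, and laboratory summaries may be left to an analysis plan. But the grading rule is fixed in this protocol, so it is not a detail awaiting the analysis plan.

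**Conclusion.** The point stands within limits. In the text shown, Appendix 2 has no numeric grading for any blood count component or for creatinine, and the scale it prescribes instead cannot place an untreated, symptom-free laboratory abnormality above mild; strictly, it gives no grade. Other laboratory values in the same table are graded by number alone, so severity is graded inconsistently, and the inconsistency reaches the reportable-event definition.

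The scope is the full blood count at the two post-vaccination safety samples, weeks 1 and 12, and creatinine at the same times if it is in the biochemical screen. It would be too strong to say that every volunteer is affected: only those with an abnormal, symptom-free, untreated value could be misgraded, and the protocol gives no basis for estimating how many.

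The conclusion assumes that the table is complete as shown and that the clauses within each fallback grade apply together.

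**What to change.** First, check the source of Appendix 2 for rows that use LLN or Dec, to confirm that none were lost. If blood count and creatinine rows are found there, the point falls away.

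If none were lost:

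- Add numeric Grade 1 to 4 rows for haemoglobin, white cells, neutrophils, lymphocytes and platelets, with cut-offs chosen by the sponsor and its laboratory.
- State what the biochemical screen contains, and add a creatinine row if it is included.
- Limit the scale under ESTIMATING SEVERITY GRADE to clinical, non-laboratory events.

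The cost is an amendment to one table and one sentence; no extra samples or visits are needed. The downside is that more low-grade laboratory abnormalities will be listed.

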#### SERIOUS OR LIFE-THREATENING Adverse Events

ANY clinical event deemed by the clinician to be serious or life-threatening should be considered a Grade 4 Adverse Event. Clinical events considered to be serious or life-threatening include, but are not limited to: seizures, coma, tetany, diabetic ketoacidosis, disseminated intravascular coagulation, diffuse petechiae, paralysis, acute psychosis, severe depression.

#### MISCELLANEOUS

- When two values are used to define the criteria for each parameter, the lowest values will appear first.
- Parameters are generally grouped by body system.
- Some protocols may have additional protocol specific grading criteria.

**APPENDIX 2 continued – Modified Table for Grading Severity of Adult Adverse Experiences  
for Vaccine Trials**

| Parameter                                              | Grade 1
Mild   | Grade 2
Moderate | Grade 3
Severe | Grade 4
Potentially
Life-Threatening |
|--------------------------------------------------------|-------------------|---------------------|-------------------|--------------------------------------------|
| POTASSIUM                                              |                   |                     |                   |                                            |
| Hyperkalemia                                           | 5.0 – 5.5 meq/L   | 5.6 – 6.0 meq/L     | 6.1 – 6.5 meq/L   | >6.5 meq/L                                 |
| Hypokalemia                                            | 3.2 – 3.4 meq/L   | 2.9 – 3.1 meq/L     | 2.5 – 2.8 meq/L   | <2.5 meq/L                                 |
| PHOSPHATE                                              |                   |                     |                   |                                            |
| Hypophosphatemia                                       | 2.0 – 2.4 mg/dL   | 1.5 – 1.9 mg/dL     | 1.0 – 1.4 mg/dL   | <1.0 mg/dL                                 |
| CALCIUM – (corrected
for albumin)                   |                   |                     |                   |                                            |
| Hypocalcemia                                           | 7.8 – 8.4 mg/dL   | 7.0 – 7.7 mg/dL     | 6.1 – 6.9 mg/dL   | <6.1 mg/dL                                 |
| Hypercalcemia                                          | 10.6 – 11.5 mg/dL | 11.6 – 12.5 mg/dL   | 12.6 – 13.5 mg/dL | >13.5 mg/dL                                |
| MAGNESIUM                                              |                   |                     |                   |                                            |
| Hypomagnesemia                                         | 1.2 – 1.4 meq/L   | 0.9 – 1.1 meq/L     | 0.6 – 0.8 meq/L   | <0.6 meq/L                                 |
| BILIRUBIN                                              |                   |                     |                   |                                            |
| Hyperbilirubinemia                                     | >1.0 – 1.5 x ULN  | >1.5 – 2.5 x ULN    | >2.5 – 5 x ULN    | >5 x ULN                                   |
| GLUCOSE                                                |                   |                     |                   |                                            |
| Hypoglycemia                                           | 55 - 84 mg/dL     | 40 – 54 mg/dL       | 30 -39 mg/dL      | <30 mg/dL                                  |
| Hyperglycemia
(nonfasting and no prior
diabetes) | 118 – 160 mg/dL   | 161 - 250 mg/dL     | 251 – 500 mg/dL   | >500 mg/dL                                 |
| Triglycerides                                          | ----              | 400 - 750 mg/dL     | 751 – 1200 mg/dL  | >1200 mg/dL                                |
| URIC ACID                                              |                   |                     |                   |                                            |
| Hyperuricemia                                          | 7.5 – 10.0 mg/dL  | 10.1 – 12.0 mg/dL   | 12.1 – 15.0 mg/dL | >15.0 mg/dL                                |
| LIVER TRANS-
AMINASE (LFTs)                         |                   |                     |                   |                                            |
| AST (SGOT)                                             | 1.25 – 2.5 x ULN  | >2.5 – 5.0 x ULN    | >5.0 – 10.0 x ULN | > 10.0 x ULN                               |
| ALT (SGPT)                                             | 1.25 – 3.0 x ULN  | >3.0 – 5.0 x ULN    | >5.0 – 10.0 x ULN | > 10.0 x ULN                               |
| GGT                                                    | 1.25 – 2.5 x ULN  | >2.5 – 5.0 x ULN    | >5.0 – 10.0 x ULN | > 10.0 x ULN                               |
| Alk Phos                                               | 1.25 – 2.5 x ULN  | >2.5 – 5.0 x ULN    | >5.0 – 10.0 x ULN | > 10.0 x ULN                               |
| PANCREATIC
ENZYMES                                  |                   |                     |                   |                                            |
| Amylase                                                | >1.0 – 1.5 x ULN  | >1.5 – 2.0 x ULN    | >2.0 – 5.0 x ULN  | >5.0 x ULN                                 |
| Pancreatic amylase                                     | >1.0 – 1.5 x ULN  | >1.5 – 2.0 x ULN    | >2.0 – 5.0 x ULN  | >5.0 x ULN                                 |
| Lipase                                                 | >1.0 – 1.5 x ULN  | >1.5 – 2.0 x ULN    | >2.0 – 5.0 x ULN  | >5.0 x ULN                                 |

APPENDIX 2 continued – Modified Table for Grading Severity of Adult Adverse Experiences  
for Vaccine Trials

| Parameter                     | Grade 1
Mild                                                                                                                                       | Grade 2
Moderate                                                                                 | Grade 3
Severe                                                                                                     | Grade 4
Potentially
Life-Threatening                                                                     |
|-------------------------------|-------------------------------------------------------------------------------------------------------------------------------------------------------|-----------------------------------------------------------------------------------------------------|-----------------------------------------------------------------------------------------------------------------------|----------------------------------------------------------------------------------------------------------------|
| CARDIOVASCULAR                |                                                                                                                                                       |                                                                                                     |                                                                                                                       |                                                                                                                |
| Cardiac Arrhythmia            | -----                                                                                                                                                 | Asymptomatic;
transient dysrhythmia,
no R x req                                    | Recurrent/persistent
dysrhythmia;
symptomatic R x req                                                | Unstable
dysrhythmia,
hospitalization and
R x req                                          |
| Hypertension                  | Transient, increase >20 mm
Hg diastolic BP; no R x req                                                                                  | Recurrent; chronic
increase >20 mm Hg
diastolic BP; R x req                        | Acute R x req; outpatient OR
hospitalization possible                                                   | Hospitalization req
OR end organ
damage                                                                  |
| Hypotension                   | Transient orthostatic
hypotension with heart rate
increased by >20 beats/min
OR decreased by <10 mm
Hg systolic BP, no R x req | Symptoms OR BP
decreased by <20 mm
Hg systolic, correctable
with oral fluid R x | IV fluid req OR
hospitalization                                                                                    | Mean arterial
pressure <60 mm
Hg, OR end organ
damage, OR
shock, vasopressor
R x req |
| Pericarditis                  | Minimal effusion                                                                                                                                      | Mild/mod
asymptomatic effusion,
no R x                                             | Symptomatic effusion, pain,
EKG changes                                                                            | Tamponade OR
pericardiocentesis
OR surgery req                                                           |
| Hemorrhage,
blood loss     | -----                                                                                                                                                 | Mildly symptomatic, no
R x req                                                        | Gross blood loss OR 1-2
units transfused                                                                           | Massive blood
loss OR >2 units
transfused                                                                |
| GASTROINTESTINAL              |                                                                                                                                                       |                                                                                                     |                                                                                                                       |                                                                                                                |
| Nausea                        | Mild OR transient;
reasonable intake maintained                                                                                                    | Mod discomfort OR
intake decreased for <3
days                                                | Severe discomfort OR
minimal intake for ≥3 days                                                                    | Hospitalization req                                                                                            |
| Vomiting                      | Mild OR transient; 2-3
episodes per day OR mild
vomiting lasting <1 week                                                                        | Mod OR persistent; 4-5
episodes per day; OR
vomiting lasting ≥ week                           | Severe vomiting of all
food/fluids in 24 hrs OR
orthostatic hypotension OR
IV R x req             | Hypotensive shock
OR hospitalization
req for IV R x req                                       |
| Diarrhea                      | Mild OR transient; 3-4 loose
stools per day OR mild
diarrhea lasting <1 week                                                                    | Mod OR persistent; 5-
10 loose stools per day
OR diarrhea lasting ≥1
week                  | >10 loose stools/day bloody
diarrhea; OR orthostatic
hypotension OR electrolyte
imbalance, >2 L IV fluid req | Hypotensive shock
OR severe
electrolyte
imbalance                                                     |
| Oral Discomfort/
Dysphagia | Mild discomfort, no
difficulty swallowing                                                                                                          | Difficulty swallowing
but able to eat and drink                                                  | Unable to swallow solids                                                                                              | Unable to drink
fluids; IV fluids
req                                                                    |
| Constipation                  | -----                                                                                                                                                 | Moderate abdominal
pain 78 hours with
impaction require
outpatient prescription            | Requiring disimpaction or
hospital treatment                                                                       | Distention with
vomiting OR
obstipation                                                                  |

